### Intervention group

The *Living in 2 Worlds* intervention groups will be facilitated by Phoenix Indian Center. During the Fall semester, youth will meet at school for 12 weeks, one hour per week, at convenient times (e.g., during lunch period). Urban Indigenous, trained facilitators from Phoenix Indian Center will deliver the *Living in 2 Worlds* curriculum.

### Comparison group

The comparison group will only complete surveys during the academic year on the same schedule as the *Living in 2 Worlds* intervention group. After RCT data collection is complete, the comparison group will have the opportunity to participate in *Living in 2 Worlds* at no cost during a summer camp implementation to ensure all adolescents have access to the curriculum.

### Survey data collection

All youth will complete a 30-min self-administered pretest questionnaire, administered electronically via a tablet, one week prior to Living in 2 Worlds beginning (T1 - September), an immediate post-test two months after implementation ends (T2 - January), at a time when the program effects on the prevention of short-term risks for vaping are expected to be strongest, and a follow-up posttest four months later (T3 – May) to assess longer-term efficacy of the intervention at the end of the school year.

### Study measures

#### Vaping behaviors

Key vaping outcomes are modeled after the Monitoring the Future survey for youths’ self-reports of recent (last 30 days) and lifetime vaping behaviors (66). Vaping nicotine will be defined as “vaping nicotine (using a JUUL, e-cigarette, e-pen)” (66) and vaping cannabis will be defined as “vaping marijuana or cannabis (e.g., using cannabis oils or liquids, dried herbs, or a cannabis concentrate, like wax, shatter, or budder)” (67). Separate but parallel questions will assess nicotine and cannabis vaping. These items include: During the last 30 days [lifetime] have you vaped nicotine [cannabis]? On how many days (if any) during the last 30 days [lifetime] have you vaped nicotine [cannabis]? Did you first start vaping nicotine [cannabis] in the last 30 days? There is sufficient evidence of the validity of self-reports and for comparing self-reports over time (68).

#### Risk factors for vaping [scales]

Measures of key risk factors for vaping will be drawn from the Monitoring the Future survey (66) and our prior *Living in 2 Worlds* study (43). Separate but parallel questions will assess nicotine and cannabis vaping. *Intentions to vape* will be assessed by asking adolescents, “If you had the chance this weekend, would you vape nicotine [cannabis]?” *Permissive norms* for vaping will be assessed for the adolescent, close friends, parents, and grandparents by asking: “Is it OK for someone your age to vape nicotine [cannabis]?; “How many of your friends would you estimate vape nicotine [cannabis];” and “How angry would your parents [grandparents] be if they found out you vaped nicotine [cannabis]?” *Vulnerability to offers* will gauge the extent to which the adolescent is confident they would decline an offer to vape from a family member, close friend, and a school peer. *Perceived benefits* of vaping will assess perceptions of the positive consequences of vaping, (e.g., whether vaping reduces nervousness or looks cool). *Perceived harms* of vaping will ask, “How much do you think people risk harming themselves (physically or in other ways) if they vape an e-liquid with nicotine [cannabis] occasionally,” and “…vape an e-liquid with nicotine [cannabis] regularly?

#### Skills acquired in *Living in 2 Worlds* [scales]

Based on our prior studies (43, 69), the *drug resistance strategies* measures will assess adolescent’s responses to vaping offers: the likelihood that they would turn down an offer (refuse); give an explanation or excuse (explain); stay away from situations (avoid); or leave the situation (leave). *Risk assessment* will gauge ways that the adolescent evaluates the risk of accepting the offer to vape including thinking about what it would do to their health, and the possibility a parent or elder might find out. Measures of *Decision-making/Problem-solving skills* will include questions concerning how the adolescent solves important problems like letting someone else decide or doing what others do. *Connections with cultural values* will be assessed through three validated instruments: American Indian ethnic identity (70), connections to American Indian spirituality (71), and involvement with American Indian cultural traditions (72).

#### Additional substance use

Youths’ self-reports of recent (last 30 days) frequency and amount of alcohol, cigarettes, marijuana (excluding cannabis vaping), and inhalants will be measured with items from the prior *Living in 2 Worlds* study (43).

### Statistical data analysis plans

Descriptive statistics will be assessed to identify data entry errors, outliers, and variable distributions. Scales with Chronbach’s *α* coefficients of at least 0.70 will be deemed sufficiently reliable to be included in further analysis. To test the hypotheses for nicotine and cannabis vaping, we will employ intent-to-treat models, separately for each substance. To examine change in outcomes between T1, T2, and T3, we will use general linear models and latent change models. Latent change models are appropriate for analyzing repeated-measures because these models adjust for measurement error, reduce estimate bias, and simultaneously assess changes within and between intervention and comparison groups, the timing of group differences, and their magnitude and direction. They can model a variety of trajectories of change and assess T1 to T2 changes separately from T2 to T3, indicating whether short-term changes in outcomes continue their trajectory, plateau or reverse direction (73). We will assess global model fit using the model chi-square; normed chi-square; comparative fix index; and root mean square error of approximation, following established cutoff criteria (74).

For all models, we will use the appropriate link function based on the level of measurement of the dependent variable. All models will control for demographic characteristics of participants where baseline equivalence between the treatment and comparison group are not achieved (e.g., sex, age, usual grades in school, two-parent household, receipt of free lunch at school), as well as control for school to adjust standard errors for the nested nature of the data (students nested in schools). Because of the small number of schools, multi-level models cannot be employed as they could lead to slightly inflated Type 1 error rates (75). We will adjust for missing data due to any attrition by employing full-information maximum likelihood (FIML) estimation. To determine if the null hypotheses should be rejected, effect sizes and their confidence intervals will assess the precision and substantive significance, and exact *p*-values will assess Type I error. We will also test if the adapted *Living in 2 Worlds* maintains effect sizes for other substance use seen in the original efficacy trial of *Living in 2 Worlds* (43). Based on a prior meta-analysis of universal substance use prevention programs for adolescents in grades 6 and 7, the overall average effect sizes were: *d* = 0.14 for smoking, *d* = 0.10 for alcohol use, and *d* = 0.14 for drug use (76). Based on this, we selected a non-inferiority margin of *d* = 0.14, which reflects approximately 50% of the effect size established in the original efficacy trial of *Living in 2 Worlds*.

We will test for moderation through interaction terms in general linear models (77) and multigroup analyses in latent change models (78). Multigroup analysis simultaneously tests separate models for each group. To test if parameter estimates of outcomes in the intervention conditions are equal across groups, we will use the chi-square difference test and compare model fit using model constraint methods for the main intervention effect path. A significant increase in chi-square between the two models (constrained-*M*_0_ vs. free-*M*_1_) indicates significant intervention effects between groups.

Sensitivity analyses will be conducted to test if the direction/magnitude of results differ based upon the sex of the youth. Although the study is powered to detect differences greater than *d* = 0.31, patterns of differences can be noted for future investigation. In addition, to respond to Phoenix Indian Center’s request to evaluate the summer camp version of *Living in 2 Worlds*, we will use a one group within-group pre-posttest design with paired t-tests (for continuous variables) or a McNemar’s chi-square test (for dichotomous variables) to examine the extent of change in vaping and associated outcomes of interest from the T3 RCT survey, which will serve as the summer camp pretest, to a post-test at the conclusion of summer camp.

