### Phase 3: Randomized controlled trial (RCT) of the vaping adaptation of living in 2 worlds

#### Randomization of schools

Ten middle schools in the Phoenix metropolitan area that have a Native American Education Program will be invited to participate in the study over the course of two cohorts (one cohort per school year). The Native American Education Program is administered by the Office of Indian Education at the Arizona Department of Education with the goal of supporting academic and culture needs of Native American students in Arizona. Schools will be randomly assigned into either: (1) *Living in 2 Worlds* Intervention (5 schools; 180 adolescents; 36 per school) or (2) Comparison group (5 schools; 180 adolescents; 36 per school).

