#### Sample size calculations

Sample size calculations for the main effects of the intervention were estimated from the average effect of cigarette and marijuana use in the original *Living in 2 Worlds* efficacy trial (*d* = 0.31) and through a systematic review of school-based e-cigarette preventive interventions (*d* = 0.47). With a sample size of 132 adolescents, an effect size *of d* = 0.31 can be detected with 0.80 power for a significant intervention difference assuming a Type I error rate of *d* = 0.31, *α* = 0.05, given a pretest R^2^ = 0.67 and a 20% attrition rate. Effect sizes for the moderation analysis were estimated comparing alcohol use of urban Indigenous students who self-identified as American Indian only to students who self-identified as multiracial/ multiethnic (OR = 1.41; *d* = 0.19) (48). Assumingα = 0.05, a pretest R^2^ = 0.67, and a 20% attrition rate, we will have 80% power to detect *d* = 0.19, for statistically significant moderated intervention effects with 360 urban Indigenous adolescents ages 11–14.

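### With ten randomised schools, the planned control for school does not give valid inference as worded, and the reason for barring multilevel models does not support that choice

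*Protocol article*

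**What the plan says.** Under Randomization of schools, the unit of allocation is the school: "Schools will be randomly assigned into either" the intervention or the comparison condition. The comparison arm is given as "Comparison group (5 schools; 180 adolescents; 36 per school", and the intervention arm has the same size.

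Under Statistical data analysis plans, the efficacy models are named: "we will use general linear models and latent change models". All models adjust for demographic variables that turn out unbalanced. The same sentence adds that they will "control for school to adjust standard errors for the nested nature of the data". The next sentence excludes random-effects modelling: "Because of the small number of schools, multi-level models cannot be employed as they could lead to slightly inflated Type 1 error rates".

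The article does not say whether controlling for school means school terms in the mean model or cluster-robust standard errors. It names no small-sample correction and no cluster-level degrees of freedom. Sample size calculations gives no ICC and no design effect.

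**The concern.** Every school lies wholly in one arm, so school and arm are not separable in the way that sex and arm are. Adding school terms beside the demographic covariates leaves no information for an arm effect, and it does not carry between-school variation into the standard error. Cluster-robust standard errors avoid the first problem, but in their usual large-sample form they are unreliable with ten clusters.

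The reason given for excluding multilevel models is the small number of schools. That affects every method for clustered data, including the one adopted.

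The rule covers all models, so every Aim 2 p-value and interval depends on it, including the non-inferiority comparison for other substances. It is a stated choice with a stated reason. An analysis plan that follows it inherits the problem, and one that departs from it contradicts the published protocol.

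**Working it through.** **Inputs.** From Randomization of schools: 10 schools, 5 per arm, 36 adolescents each. From Sample size calculations: 20% attrition (36 × 0.8 = 28.8, about 29 analysed per school), pretest R² = 0.67, α = 0.05, 80% power, d = 0.31 and d = 0.19. ICC: not stated, so 0.01 to 0.10 is assumed.

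**1. Is clustering allowed for in the sample size?** The article says "With a sample size of 132 adolescents" an effect of d = 0.31 "can be detected with 0.80 power for a significant intervention difference". The individual-randomisation formula is n per arm = 2(1.96 + 0.84)²(1 − R²)/d².
- d = 0.31: 54 per arm, 108 in total. This is 135 after dividing by 0.8, or 130 after multiplying by 1.2. The stated 132 is within 3% of either.
- d = 0.19: 144 per arm, 288 in total, and 288/0.8 = 360, an exact match.

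Both figures reproduce with a design effect of 1, so the sample size does not absorb clustering.

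**2. School as a covariate.** An intercept, arm and 9 school indicators make 11 columns of rank 10. Arm is a sum of school indicators and has no identified coefficient. If software drops one more indicator, the arm coefficient becomes a contrast between two reference schools. Its true variance exceeds the model variance by the factor 1 + m·ICC/(1 − ICC), so Type I error = 2[1 − Φ(1.96/√factor)]. With m = 29:
- ICC 0.01: factor 1.29, error 8.5%
- ICC 0.02: factor 1.59, error 12.0%
- ICC 0.05: factor 2.53, error 22%
- ICC 0.10: factor 4.22, error 34%

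**3. No between-school variance in the standard error.** Error = 2[1 − Φ(1.96/√(1 + (m − 1)ICC))]. With m = 29 this is 8.3%, 11.7%, 20.6% and 31.5% at the same four ICCs.

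**4. Simulation under no effect.** Continuous outcome, 4,000 runs per setting. Ranges cover 29 and 36 pupils per school. The Monte Carlo standard error near 5% is √(0.05 × 0.95/4000) = 0.3 points.

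| Analysis | ICC 0.01 | 0.02 | 0.05 | 0.10 |
|---|---|---|---|---|
| School indicators, redundant one dropped | 9.0-9.3% | 12.1-13.4% | 22.0-24.6% | 33.6-37.8% |
| No between-school variance in SE | 8.3-9.2% | 12.2-12.3% | 20.0-23.5% | 32.6-37.0% |
| Cluster-robust, unscaled, z | 11.4-11.8% | 11.4-12.6% | 11.8-12.0% | 12.2-12.4% |
| Cluster-robust, scaled, z | 10.0-10.2% | 9.5-11.0% | 10.2% | 10.7-10.8% |
| Cluster-robust, scaled, t on 8 df | 5.9-6.2% | 5.2-6.6% | 6.0-6.9% | 6.2-6.4% |
| Random school intercept, z | 5.1-5.8% | 6.2-7.2% | 7.8-8.6% | 9.0-9.1% |
| Random school intercept, t on 8 df | 2.2-2.8% | 3.0-3.7% | 4.2-5.0% | 4.6-5.0% |
| t-test on school means, 8 df | 4.9% | 4.2-5.5% | 4.8-5.4% | 4.7-5.0% |

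At ICC 0 the random-intercept model gives about 4% with z and 1.3-1.5% with 8 df.

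**5. Is valid inference affordable?** With SE = √0.33 × √(4·DE/N), DE = 1 + (m − 1)ICC and a t test on 8 df, take d = 0.31 and 28.8 to 36 analysed per school. Power is 0.94-0.97 at residual ICC 0.01, 0.89-0.93 at 0.02 and 0.74-0.77 at 0.05.

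**The case against.** The stated purpose of the school term is to adjust standard errors, which fits cluster-robust estimation as well as it fits fixed school terms. Under that reading nothing is collinear, and with finite-sample scaling and t on 8 df the error is about 5-7%, comparable with the multilevel z test. A condensed article may leave the exact estimator to a fuller document. **This stands.** A reader might infer that the arm effect simply cannot be estimated; the article does not support that without the condition that school enters as a covariate. Even then, a stacked repeated-measures model could estimate an arm-by-time term, although its standard error would still omit between-school variation in change.

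A reader might also infer that the adopted approach has a far larger Type I error than the rejected one. That holds only for the covariate or unadjusted reading, and only if the ICC is about 0.05 or more. No document value supports such an ICC, and the relevant one is for the outcome after pretest adjustment. At 0.01 the error is 8-9%.

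The premise about multilevel models is not false either: the z version does run to about 9%. The fault lies in the step from that premise to exclusion.

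The objection does not remove the defect. The exclusion is stated outright, and no few-cluster correction accompanies the method put in its place.

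**Conclusion.** The concern holds in conditional form. As worded, the control for school is one of two things:
- a covariate collinear with arm, which leaves the effect on an outcome or change score unidentified; or
- a few-cluster standard-error adjustment with no stated small-sample correction, with Type I error about 10-13%.

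The method ruled out gives about 4-9% uncorrected and at most about 5% on 8 df. The small number of schools is therefore a reason to correct for few clusters, not to exclude multilevel models.

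The sizes rest on assumed ICCs, equal school sizes and a continuous outcome; binary outcomes were not simulated. The collinearity needs no ICC. The cluster-robust result barely changes across the ICCs tried.

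**What to change.** 1. Remove school as a fixed control variable and delete the sentence excluding multilevel models.
2. For continuous outcomes, make the confirmatory test a random-school-intercept model adjusted for the T1 value, with Kenward-Roger or Satterthwaite degrees of freedom (about 8).
3. For binary outcomes such as initiation and 30-day vaping, where Kenward-Roger does not carry over directly, use a school-level analysis of T1-adjusted summaries on about 8 df, or a permutation test over the school allocation. Schools enter in two cohorts, so the permutation set must respect any stratification by cohort. Unrestricted 5 v 5 allocation has 252 arrangements; stratification leaves fewer.
4. Keep the latent change models if their standard errors carry a few-cluster correction. Otherwise label them supportive.

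**Cost.** Wording and code, and no new data. Intervals widen. Compared with a standard error that ignores schools, the 8-df critical value alone adds 2.306/1.96 = 1.18. With √(1 + 28 × 0.02) = 1.25 at ICC 0.02, the total is 1.18 × 1.25 = about 1.5 times the width. The 8-df mixed model is somewhat conservative at low ICC.

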## Introduction

The US Surgeon General declared adolescent e-cigarette vaping an epidemic in 2018 (1) due to the 13-fold increase in only 7 years (2). Indigenous adolescents have the highest prevalence and earliest initiation of nicotine vaping of all racial/ethnic groups (3, 4). Almost half of Indigenous youth report past 30-day nicotine vaping as compared to 32.7% of US youth, and Indigenous high school students are twice as likely than other students to be frequent e-cigarette users (5). While there remains a critical need to prevent nicotine and cannabis vaping among Indigenous adolescents, prevention efforts are particularly challenging due to the unique features of vaping such as ease of concealability, ability to purchase online, and perceptions of fewer adverse health consequences (6).

In the US, the Bureau of Indian Affairs officially recognizes 574 tribes (7), each with its own distinct cultural practices, languages, and traditions, reflecting the rich diversity among Indigenous peoples. This variation is also present in urban areas, where approximately 60% of Indigenous individuals live (8). Although Indigenous adolescents are exposed to influences in multiple domains (peers, family, school, and community) that can increase their risk of vaping, in the urban environment these risk factors may be amplified by the complex navigation of ethnic identity, due to geographic dispersion, cultural disconnections, and persistent discrimination (9, 10). Compared to the general urban population, urban Indigenous families experience lower socioeconomic status, employment, education, and residential stability (11). They are more likely to move frequently within urban areas and/or move between urban areas and reservation lands for short periods of time (12, 13). This pattern of mobility is not unique to urban Indigenous populations but reflects a broader pattern of geographic fluidity among many tribal communities, where individuals and families move between urban centers and tribal homelands for cultural, familial, or economic reasons (14). As a consequence, many urban Indigenous adolescents experience cultural disconnection from their ancestral homelands and have less understanding of their own tribes’ practices and traditions than tribal youth (15–18).

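### FIML does not adjust for attrition in a general linear model with one follow-up outcome, and the imbalance-triggered covariate rule picks demographics on a criterion unrelated to loss

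*Protocol article*

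**What the plan says.** All statements here are in the protocol article, section Statistical data analysis plans, unless noted.

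- Models: "To examine change in outcomes between T1, T2, and T3, we will use general linear models and latent change models". The latent change models are described as able to "assess T1 to T2 changes separately from T2 to T3". The article does not say whether the general linear models take one follow-up outcome or all waves together. Both classes also carry the moderation test.
- Missing data: "We will adjust for missing data due to any attrition by employing full-information maximum likelihood (FIML) estimation". Neither model class is singled out and no auxiliary variables are named.
- Covariates: "All models will control for demographic characteristics of participants where baseline equivalence between the treatment and comparison group are not achieved". The examples are sex, age, usual grades, two-parent household and free school lunch. School is controlled in all models without this condition.
- Sample size calculations: pretest R² = 0.67 and 20% attrition, with d = 0.31 for the main effect and d = 0.19 for moderation. The analysis section sets a non-inferiority margin of d = 0.14 for other substance use.
- Introduction, on urban Indigenous families: "They are more likely to move frequently within urban areas and/or move between urban areas and reservation lands for short periods of time".

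**The concern.** Two statements work less well than they read.

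First, FIML gains over complete-case analysis only when a pupil with a missing outcome has other modelled data that inform it. A regression of one follow-up score on arm and baseline variables contains no such data, so there the promised adjustment adds nothing.

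Second, what protects a likelihood analysis against selective loss is having the predictors of loss and outcome in the model. The stated rule instead selects demographics by whether the arms happen to differ at T1. A variable can be balanced at T1 and still drive dropout differently in the two arms.

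The article expects 20% attrition in a mobile population. One arm meets weekly for 12 weeks and the other only completes surveys, so different patterns of loss by arm are possible. The arm effect would then carry a bias that data already collected could remove.

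**Working it through.** **1. The plan's own figures.** Inputs: d = 0.31, R² = 0.67, power 0.80, 20% attrition (Sample size calculations); two-sided α = 0.05 is assumed.

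n per arm = 2(1 − R²)(1.960 + 0.842)²/d² = 2 × 0.33 × 7.849/0.0961 = 53.9, so 54 per arm and 108 in total. Then 108/0.8 = 135, against 132 stated; power at 132 is 0.792.

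For d = 0.19: 5.180/0.0361 = 143.5, so 144 per arm, 288 in total, and 288/0.8 = 360 as stated.

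The figures are close enough to show that the plan counts on adjustment for the pretest. Bias should therefore be judged with T1 in the model.

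**2. FIML with one outcome.** A pupil with predictors x and missing y contributes ∫ f(y | x, β) dy = 1 to the likelihood, whatever β is. Only completers inform the arm effect. In simulation (N = 360, about 20% of T3 missing, 400 runs per mechanism), single-outcome FIML and complete-case estimates agreed to below 1e-10 in every run.

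**3. FIML with T2 and T3 modelled jointly given arm and T1.** Same simulation, true T3 effect −0.155, Monte Carlo error about 0.0035. Coefficients and loss mechanisms are assumptions.

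| Loss depends on | Bias, single-outcome FIML (= complete case) | Bias, joint FIML |
|---|---|---|
| nothing | 0.002 | 0.002 |
| T1 outcome | 0.001 | 0.000 |
| T2 outcome | −0.017 | −0.002 |
| omitted baseline variable, opposite direction by arm | −0.089 | −0.051 |
| same, variable entered | 0.001 | 0.000 |

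Joint modelling removes the bias from loss that depends on T2. It only partly removes the bias from an omitted baseline predictor.

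**4. Size with T1 in the model.** Assumptions: continuous outcome, true effect 0, 20% lost in each arm, T1–outcome correlation √0.67 = 0.82, and log-odds of loss rising by 1 per SD of a baseline predictor W in the comparison arm and by 0 in the intervention arm.

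Without T1 in the model, bias is 0.052 when W correlates 0.3 with the outcome and 0.083 when it correlates 0.5. The gap in mean W between the retained groups is then δ ≈ 0.052/0.3 ≈ 0.083/0.5 ≈ 0.17 SD. With T1 in the model, approximately:

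bias ≈ δ × (r_WY − 0.82 × r_WT1)

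The formula and a check by simulation (N = 360, 3,000 runs per cell, Monte Carlo error about 0.001) give:

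| r_WY | r_WT1 | Formula, one arm | Simulated, one arm | Simulated, opposite by arm |
|---|---|---|---|---|
| 0.3 | 0.3 | 0.17 × 0.054 = 0.009 | 0.008 | 0.018 |
| 0.3 | 0.2 | 0.17 × 0.136 = 0.023 | 0.023 | 0.049 |
| 0.5 | 0.5 | 0.17 × 0.090 = 0.015 | 0.016 | 0.030 |
| 0.5 | 0.35 | 0.17 × 0.213 = 0.036 | 0.037 | 0.074 |
| 0.5 | 0.2 | 0.17 × 0.336 = 0.057 | 0.057 | 0.118 |

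With the same slope in both arms, simulated bias was within 0.001 of 0. With W entered it was within 0.002 of 0 in every cell.

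**5. Against the plan's reference values.** A bias of 0.06 is 0.06/0.31 = 19% of the main-effect d and 0.06/0.14 = 43% of the non-inferiority margin. A bias of 0.12 is 39% and 86%. A bias of 0.01 is 3% and 7%.

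**The case against.** The best defence is that the FIML sentence is right where it matters most. The latent change models, which the article describes at length, carry T1, T2 and T3 together, and FIML there uses the partial records. The general linear models are never said to have a single outcome, and fitted jointly over the waves they would not reduce to complete cases. This stands, and it makes the first half of the point conditional on model form.

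A reader might infer that the covariate rule keeps predictors of attrition out of every model. It does not. The rule covers demographics only, school is always included, earlier waves are in the latent change models, and race/ethnicity enters the moderation models. T1 use of the other substance is not a demographic, so the rule neither admits nor excludes it.

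A reader might also infer a bias of 0.05 to 0.13 SD set against d = 0.19. Those sizes arise only without the T1 outcome in the model, and the largest uses a correlation of 0.82, which is in effect the pretest itself. The 0.19 is the moderation effect; the main-effect figure is 0.31.

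Nor do the documents say that loss will differ by arm. The comparison group is surveyed on the same schedule, in school, and the youth survey incentives are stated without distinction by arm.

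Finally, a list of FIML auxiliary variables and a report of retention by arm are details that an article may leave to a fuller plan. Their absence is not an error. What remains is an unqualified claim and a stated selection rule, and neither is a mere omission.

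**Conclusion.** The point holds in a limited form. For any general linear model with one follow-up outcome, observed predictors and no auxiliary variables, the stated FIML adjustment is complete-case analysis under another name. Complete-case analysis is not in itself biased: if loss depends only on variables in the model, the estimate is sound. The balance-triggered rule for demographics uses the wrong criterion for handling loss, and this can affect the latent change models too.

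With T1 in the model, the residual bias is about 0.01 to 0.06 SD if loss follows an omitted predictor in one arm only. It is up to about 0.12 if the relation is opposite in the two arms, and about 0 if it is the same in both. These sizes rest on an assumed predictor–outcome correlation of 0.3 to 0.5, a predictor–T1 correlation of 0.2 to 0.5, a log-odds slope of 1 and a continuous outcome. A predictor less correlated with T1 would leave more bias. The lower end is negligible; the upper end matters for d = 0.31 and more so for the margin of 0.14. The sign depends on which arm loses its higher-risk pupils.

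**What to change.** 1. Fit the arm comparisons jointly over T1, T2 and T3, so that FIML uses the observed waves. Otherwise, state that single-outcome general linear models are complete-case given their covariates, and limit the FIML sentence to the joint models.
2. Replace the imbalance-triggered rule with a prespecified set used whatever the baseline balance, entered as covariates or as FIML auxiliary variables: the T1 outcome, T1 vaping of both substances, age or grade, sex, usual grades, household structure and free lunch.

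The cost is a change of wording and a few extra parameters, with 360 × 0.8 = 288 pupils expected at follow-up. If that is a burden for sparse outcomes, the auxiliary-variable route leaves the arm comparison itself unchanged. The article already lists these variables as demographic controls or survey items, so no new data are needed.
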